### Secondary outcome

The secondary outcomes include an improvement in dietary patterns (i.e., a reduction in fat food and increase in consumption of fruits and vegetables), smoking habits (i.e., a reduction in the number of cigarettes smoked per day), sleeping habits (i.e., regular number of hours slept per night), physical activity (i.e., increasing in time spent walking per day), personal and social functioning (i.e., level of functioning and time dedicated to meeting friends), severity of physical comorbidities (i.e., reduction at the CIRS global score), and adherence to medications (i.e., reduction in changes in pharmacological doses and regimen).

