## Statistical analyses

### Sample size and power calculation

A power analysis has been implemented in order to define the sample size needed to detect a significant BMI reduction (primary study's outcome) between the two groups. In particular, it has been estimated a sample size needed to observe a mean difference between the two groups of at least one point at the BMI (kg/m^2^) (with standard deviation of 2), with power set at 90% and a significant two-tailed alpha level of 0.05, based on previous studies on the same topic [e.g., (21, 23)].

Taking into account the multicenter design of the study, sample size has been adjusted for the Intercluster Correlation Coefficient (ICC), set at 0.030, and for the coefficient of variation of cluster sizes (COV), set at 0.400 (55). Therefore, the sample size consists of 348 patients (29 patients per arm in each center). Each center is expected to recruit 58 patients, rounded to 60. Moreover, previous trials evaluating the efficacy of interventions focused on physical activities and diet reported a drop-out rate of 15%; thus, the sample size has been rounded to 35 patients per arm for each center. Therefore, the expected sample size consists of 420 patients (70 patients for each participating center). This sample size has been considered feasible by all participating centers (Figure 1).

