The implementation of a generalized estimated equation model (GEE). The GEE provides an estimation of the longitudinal impact of the interventions on primary and secondary outcomes, controlling for confounders, such as physical comorbidities, severity of psychiatric symptoms, level of social functioning, quality of life, self-esteem, recovery style, support from social network. A generalized estimating equation model will be employed using the following outcomes variables: the BMI, the severity index of the Cumulative Illness Rating Scale, the abdominal circumference: plasma levels of glucose, insulin, triglycerides, and cholesterol levels (total, LDL, and HDL); systolic and diastolic blood pressure, and cigarettes smoked per day.The development of a Structural Equation Model (SEM) in order to identify possible mediators and moderators of the efficacy of the interventions, controlling for several confounders such as age, gender, severity of symptoms, BMI, etc. In particular, the variable “duration of the intervention” will be tested as one of the most relevant mediator or moderator for the efficacy of the interventions.The implementation of multivariable logistic regression models, in order to identify predictors of positive response for changing unhealthy behaviors. In particular, as regards the primary outcome, this will be transformed in binary variable (yes vs. no) using the reduction of at least 1 point at the BMI as threshold. The impact of possible predictors (e.g., having an healthy diet; walking at least 30min per day; quitting smoking) as well as confounders (such as age, gender, level of education, diagnosis, duration of the illness, type of pharmacological treatment received) will be tested in a logistic regression model.A subgroups analysis, according to the different diagnostic groups, in order to identify different profiles of efficacy of the interventions. The hypothesis is that patients suffering from affective disorders (both major depression and bipolar disorders) will report a higher improvement in the reduction of BMI and in changing their unhealthy lifestyle behaviors compared to patients with schizophrenia.

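### The diagnostic subgroup hypothesis compares improvement between diagnoses instead of the arm effect within each, so it cannot show differential efficacy; the response predictors also need a baseline time point

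*Protocol article*

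**What the plan says.** Two secondary analyses in the protocol article's Data analysis section are at issue.

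- **Subgroups.** The purpose given is to identify how the efficacy of the interventions differs by diagnosis. The hypothesis is that patients with affective disorders (major depression and bipolar disorder) "will report a higher improvement in the reduction of BMI and in changing their unhealthy lifestyle behaviors compared to patients with schizophrenia".
- **Predictors of response.** Multivariable logistic models are to find predictors of a positive response. BMI is handled as follows: "this will be transformed in binary variable (yes vs. no) using the reduction of at least 1 point at the BMI as threshold". Example predictors are "e.g., having an healthy diet; walking at least 30min per day; quitting smoking". The example confounders are demographic and clinical, and include diagnosis and drug treatment. Randomised arm is not among the examples, but both lists are open.

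Four other places bear on this:

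- Patients' recruitment stratifies by centre, age, gender and education, not by diagnosis.
- Secondary outcome lists diet, walking and smoking as outcomes, the last as "smoking habits (i.e., a reduction in the number of cigarettes smoked per day". Table 1 makes the same three behaviours targets of the experimental intervention.
- The Discussion names drug treatment, in particular second-generation antipsychotics, as something that can change BMI.
- In Aims, aim 1 concerns factors linked to poor response, aim 2 mediators and moderators, and aim 3 a description of differences in improvement between diagnostic groups.

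**The concern.** A statement that an intervention works better in one diagnosis is about the difference between arms: is that difference larger in affective disorders than in schizophrenia? The hypothesis as worded asks which patients improve more. Patients in the two diagnostic groups may differ in medication, illness course and starting weight, so one group can lose more BMI in both arms while the advantage of the experimental arm is the same in each. A test of the stated hypothesis would then be significant, and the stated purpose invites the reader to call it differential efficacy. Aim 5 is to develop guidelines for routine care, so such a claim could travel beyond the paper.

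The predictor model has a related weakness. If quitting smoking, diet and walking are measured during the trial, they are things that the intervention is meant to change. Their association with BMI loss then describes changes that occur together, or steps on the way to BMI loss. It does not identify, at the start, who will respond poorly, which is what aim 1 asks.

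**Working it through.** **1. The plan's own figure.** Inputs from Sample size and power calculation: "a mean difference between the two groups of at least one point at the BMI", SD 2, 90% power, "significant two-tailed alpha level of 0.05", ICC 0.030, coefficient of variation of cluster size 0.400, six centres, 15% dropout.

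- Unadjusted n per arm = 2 × 2² × (1.96 + 1.2816)² / 1² = 84.06, so 85.
- Design effect with 29 per arm per centre = 1 + ((1 + 0.4²) × 29 − 1) × 0.03 = 1.979.
- 85 × 1.979 = 168, within the planned 6 × 29 = 174 per arm (348 in total); power is 91%.
- 29 / 0.85 = 34.1, so 35 per arm per centre, and 35 × 12 = 420.

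The sample size stands, and nothing below touches it.

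**2. The two contrasts side by side.** Take 348 patients, SD of BMI change 2, half in each diagnosis (87 per arm within each diagnosis), clustering ignored. The even split is an assumption; the document gives no diagnostic mix.

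- Between diagnoses, arms pooled: SE = 2 × √(1/174 + 1/174) = 0.214.
- Arm by diagnosis: SE = 2 × √(4/87) = 0.429, twice as large.

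Now let the arm effect be 1 point in both diagnoses (no interaction), and let affective patients improve by 1 point more in both arms. The 1-point natural difference is an assumption chosen to show the mechanism.

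- Between-diagnosis contrast: 1 / 0.214 − 1.96 = 2.70, so it is significant with probability 0.997. A simulation of 4,000 trials gave 99.6%.
- Interaction: the simulation gave 4.8%, the nominal error rate.
- With a natural difference of 0.5 point, the between-diagnosis contrast is still significant in about 65% of trials.

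**3. Precision of the correct contrast.** The formula is SE = 2 × √(2/a + 2/b), where a and b are the patients per arm in each diagnostic group.

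| Affective share (assumed), N = 348 | SE | Difference in effect for 80% power: SE × (1.96 + 0.84) | Power for a 1-point interaction | Power for a 0.5-point interaction |
|---|---|---|---|---|
| 50% | 0.429 | 1.20 | 65% | 21% |
| 60% | 0.438 | 1.23 | 63% | 21% |
| 70% | 0.468 | 1.31 | 57% | 19% |

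With 420 × 0.85 = 357 completers and an even split, the SE is 2 × √(4/89.25) = 0.423. The range is therefore about 0.42 to 0.47.

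**4. Time point of the predictors.** The protocol gives none for any of the three. Diet and walking are worded as states and are measured at T0 (Table 3), so they may be baseline values. Quitting is worded as an event and most naturally falls after randomisation. The lifestyle questionnaire, also given at T0, does record past attempts to quit.

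**5. The 1-point cut.** With SD 2, P(fall ≥ 1) is Φ(−0.5) = 31% for a patient with mean change 0, and 50% for mean change −1. For an arm comparison, with control mean change assumed anywhere from +0.5 to −1.0, the cut raises the required n per arm from 85 to 133–147. At the planned effective size (174 / 1.979, about 88 per arm), power drops from 91% to 71–75%. These figures are for an arm comparison, which the logistic model is not said to make. The loss for the named predictors cannot be computed from the document.

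**The case against.** Much can be said for the plan.

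- Both arms are active, so describing improvement by diagnosis under the two interventions is coherent, and it is exactly what aim 3 asks. This stands: the conflict is only with the efficacy purpose stated for the subgroup analysis.
- An interaction term is a model detail that an article may leave to the full plan. This stands for the term itself. It does not rescue a stated hypothesis that names the wrong contrast.
- A reader might infer that the predictor model definitely uses post-randomisation variables and omits the arm. The text does not support that: no time points are given, both lists are illustrative, and a secondary outcome can have a legitimate baseline value. What stands is that quitting smoking is most naturally a later change and that the time point needs fixing.
- A reader might also call the 1-point cut a mistake because it equals the expected difference between arm means. The document gives no such rationale, and a responder cut in a secondary model loses precision without making the answer wrong.
- Low power for the interaction is a cost of the correct question, not a fault in the text. This stands.

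**Conclusion.** The subgroup hypothesis does not match its stated purpose. Tested as written, it can be significant almost always (99.6% in the example) when the arm effect is the same in both diagnoses. That figure rests on an assumed 1-point natural difference, SD 2, an even split and no clustering. A smaller natural difference gives a lower rate, but the contrast still measures something other than differential efficacy.

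The predictor point holds in part: time points are unstated and one example is most naturally post-randomisation, which matters for aim 1.

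It is tempting to conclude that aims 1 to 3 would all be answered wrongly. The document does not support that. Aim 2 is assigned to a separate structural equation model, and aim 3 is descriptive as worded. The primary GEE and the sample size are untouched. This is a worthwhile correction to secondary analyses.

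**What to change.** - Restate the subgroup hypothesis as an arm-by-diagnosis interaction in the BMI model, affective disorders against schizophrenia as the plan names them. Report the arm effect with its 95% confidence interval in each group, and label the analysis exploratory. The comparison of improvement between diagnoses can stay as a description for aim 3.
- For aim 1, restrict predictors to T0 values and include randomised arm. Add arm-by-predictor terms wherever response to the intervention is claimed. Report quitting smoking and changes in diet or walking during the trial as mediators or concurrent outcomes.
- Optionally, model BMI as continuous with baseline adjustment and keep the 1-point responder rate as a descriptive table.

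The cost is wording and a few model terms, with no new data. The price is visible imprecision: a difference in effect of about 1.2 to 1.3 points, larger than the whole planned arm effect of 1 point, is needed for 80% power, so a null interaction will not show that the effects are equal.

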## Stepwise procedure

From month 1 to 6, the following phases have been carried out: (1) development of the work plan for data collection in each participating center; (2) training course for mental health professionals on the interventions; (3) training course for researchers on assessment tools. From month 7 to 12, patients' recruitment has been implemented. From month 7 to 18, interventions are being provided to participating patients. From month 7 to 30, patients' follow-up assessments are being made. From month 31 to 36, statistical analyses will be performed as well as findings will be disseminated through papers and participation in conferences. The stepwise procedure is summarized in Figure 2.

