## Aims

The LIFESTYLE trial aims to evaluate the efficacy of a new psychosocial group intervention focused on healthy lifestyle behaviors compared to a psychoeducational brief group intervention in a community sample of patients with severe mental disorders on several variables including BMI, comorbidity index, smoking habits, and dietary patterns.

The secondary aims of the trial are: (1) to identify predictive factors associated with poor response to the interventions; (2) to define the role of mediators and moderators for the efficacy of the interventions; (3) to describe differences according to diagnostic groups in terms of improvement of lifestyle behaviors; (4) to evaluate the long-term effects of the interventions and their cost-effectiveness; (5) to develop guidelines for improving healthy lifestyle in people with severe mental disorders in the clinical routine care.

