### Patients' recruitment

Patients are being recruited in six outpatient units from the universities of Naples, Bari, Genova, L'Aquila, Pisa, and Rome—Tor Vergata.

Eligible patients are identified by their clinicians and referred to the LIFESTYLE research staff by phone, email, or in-person contact. After the patients have been contacted, a meeting is arranged at the outpatient clinic with the referring clinician and the LIFESTYLE staff. Verbal and written information about the project are provided. If the patient accepts to participate to the study, an informed consent form is signed and an appointment for baseline assessment is made. Once the informed consent is collected, the patient is formally enrolled in the study's protocol. Before starting the baseline assessment, the LIFESTYLE staff member contacts the statistician working at the Coordinating Center for obtaining the randomization code for patients' group allocation. The randomization procedure is stratified according to center, age, gender, and educational level with a 1:1 ratio. The treating psychiatrist will continue to provide the usual treatment to patients.

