## Assessment time and instruments

Researchers participating to the study are blinded to patient allocation. All patients are assessed at the following time points: baseline (T0); 2 months post-randomization (T1); 4 months post-randomization (T2); 6 months post-randomization (T3); 12 months post-randomization (T4); and 24 months post-randomization (T5). T1 and T2 assessments include only anthropometric tests. All data will be collected through a paper and pencil interviewing and the expected time for filling in all assessment tools is about 60/90 min. During the completion of the assessment battery, whether patients feel distressed or exhausted, the assessment can be stopped and another appointment will be scheduled in the next 2/3 days with the researcher.

The following questionnaires and schedules will be used during the study (Table 3):

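### The follow-up window closes at project month 30, but the 24-month visit (T5) falls due in about months 31 to 36, after the window for essentially all patients

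*Protocol article*

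**What the plan says.** The Stepwise procedure section of the protocol article divides the project into phases by month. For recruitment it says "From month 7 to 12, patients' recruitment has been implemented". For assessments it says "From month 7 to 30, patients' follow-up assessments are being made". For the last phase it says "From month 31 to 36, statistical analyses will be performed", together with dissemination.

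The section on assessment time and instruments counts visits from randomization. It begins "All patients are assessed at the following time points: baseline (T0); 2 months post-randomization (T1" and its last two visits are "12 months post-randomization (T4); and 24 months post-randomization (T5". The Abstract repeats this schedule. Table 3 marks every instrument at T5 except the socio-demographic schedule, the SCID-5 and the ECG, which are baseline only.

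The Aims section lists as its fourth secondary aim "to evaluate the long-term effects of the interventions and their cost-effectiveness". The Data analysis section says that missing data will be handled by LOCF. It gives no date for closing the database.

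**The concern.** The calendar and the visit schedule are both explicit, and they do not agree. A window that opens in month 7 and closes with month 30 holds exactly 24 months. That is enough for one patient's full follow-up only if the patient enters on the first day, and it adds nothing for the six months over which patients are recruited.

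Two things are at stake. If assessments stop at month 30, T5 is lost because of the calendar and not because patients drop out, and the trial has no 24-month evidence. If T5 visits go ahead when due, they occupy the same six months that the plan gives to analysis and dissemination, so the final analysis would start before the last data are in. The plan does not say which of these is intended.

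**Working it through.** **Inputs**

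- Recruitment: months 7 to 12 (Stepwise procedure).
- Follow-up assessments: months 7 to 30 (Stepwise procedure).
- Analysis and dissemination: months 31 to 36 (Stepwise procedure).
- Visits after randomization: T3 at 6 months, T4 at 12, T5 at 24 (Assessment time and instruments; Abstract; Table 3).
- Start of the clock: after consent and before the baseline assessment, staff request the allocation. The Patients' recruitment section says that a staff member "contacts the statistician working at the Coordinating Center for obtaining the randomization code for patients' group allocation". Randomization therefore cannot come before recruitment opens in month 7.

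**Formula.** Project month of a visit = month of randomization + months after randomization.

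| Month randomized | T3 (+6) | T4 (+12) | T5 (+24) | T5 month minus 30 |
|---|---|---|---|---|
| 7 | 13 | 19 | 31 | 1 |
| 8 | 14 | 20 | 32 | 2 |
| 9 | 15 | 21 | 33 | 3 |
| 10 | 16 | 22 | 34 | 4 |
| 11 | 17 | 23 | 35 | 5 |
| 12 | 18 | 24 | 36 | 6 |

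T3 and T4 lie inside months 7 to 30 for every month of entry. T5 lies outside it for every month of entry. The stated close at month 30 is therefore not reproduced; the inputs give 12 + 24 = month 36.

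**The boundary.** Months 7 to 30 inclusive are 30 − 7 + 1 = 24 months. A patient randomized on the first day of month 7 completes 24 months on the first day of month 31, one day after the window closes. A patient randomized on the first day of month 12 has 30 − 12 + 1 = 19 months inside the window, so T5 comes about five months after the close. For a patient randomized at the end of month 12, the gap is about six months.

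**Overlap with analysis.** T5 runs from 7 + 24 = month 31 to 12 + 24 = month 36. That is the whole of the analysis and dissemination phase.

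**The case against.** Four points can be made for the plan.

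*The miss is one day for the earliest patients.* This stands. The article gives no visit windows, and a condensed article may leave them to the full protocol. With an ordinary tolerance, patients randomized at the very start of month 7 could have T5 within month 30. A reader might infer that not one patient can reach T5 in time, but that claim rests on the one-day margin. For patients randomized in months 8 to 12 the shortfall is at least a month on any count.

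*Long-term need not mean 24 months.* This stands too. A reader might infer that the fourth secondary aim cannot be met. The Aims section does not define long-term, and T4 fits for everyone. The intervention lasts 5 months, so T4 observes patients about 12 − 5 = 7 months after it ends. Nor does the text tie cost-effectiveness to T5. Only the 24-month part is at risk.

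*Nothing says that the data close at month 30.* This is correct. A reader might infer that LOCF will fill all T5 values from T4 or earlier, so that a reported 24-month effect would be the 12-month effect under another name. That would follow only if the data were closed at month 30 and the LOCF rule were then applied to T5. No lock date is given, and T5 visits could equally continue into months 31 to 36.

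*It is only a project timetable, and Figure 2 may differ.* Figure 2 was not available to check. The section says that it summarizes the same procedure, so it cannot correct the written dates by itself. The timetable also matters, because it says when assessments end and when analysis begins.

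**Conclusion.** The inconsistency is real and is confined to T5. On the stated dates, T5 falls in about months 31 to 36, after the month-30 close for essentially all patients, by between one day and about six months. It also coincides with the entire analysis phase. Nothing in the article reconciles the two.

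The primary outcome, BMI at T3, is due in months 13 to 18, and T4 is due in months 19 to 24. Both fit, so the primary comparison is untouched. The loss is the 24-month part of the long-term aim. The LOCF harm is conditional on a data closure that the plan does not state.

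The conclusion assumes that project months are consecutive calendar months, that recruitment keeps to months 7 to 12, and that T5 is held when due, since no visit tolerance is given. It should be fixed before any 24-month result is planned or claimed, but it is not a flaw that undermines the trial's main result.

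**What to change.** Reconcile the Stepwise procedure section (and Figure 2, if it repeats the same dates) with the visit schedule, in one of two ways.

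1. **Keep T5.** Run follow-up assessments from month 7 to month 36. Analyse T3 and T4 in the existing analysis window and date the T5 analysis after month 36. No visits are added to those already planned. The cost is that T5 reporting runs past the stated 36-month project. Because the statistician is to be blinded during the trial, the revised timetable should also say how that is kept while T5 is outstanding and the T3 and T4 analyses are under way.
2. **Drop T5.** State 12 months as the longest follow-up in the Abstract, the assessment schedule and Table 3. The cost is a weaker long-term claim.

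Under either option, state that LOCF will not be used for T5 visits that are missing only because follow-up closed before they were due. How to treat T5 values missing through ordinary dropout is a separate question that this change does not settle.
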